## Methods/design

The design of the study will be placebo-controlled, single-blind, randomized, stratified by centre and by the length of gestation: <49 days; 50–56 days; 57–63 days. A total of 3008 women with pregnancies of < 63 days from last menses (verified by ultrasound) will be recruited for the study in participating centres (188 subjects per centre; 62–64 per each strata of gestation) from among women requesting legal termination of pregnancy and who prefer medical abortion. All subjects will get 200 mg mifepristone orally, and 24 (+/- 2) hours later they will receive either: 4 placebo tablets vaginally and 2 tablets of misoprostol and 2 placebo tablets sublingually; or 4 placebo tablets vaginally and 4 tablets of 200 μg misoprostol sublingually; or 2 tablets of 200 μg misoprostol plus 2 placebo tablets vaginally and 4 placebo tablets sublingually; or 4 tablets of 200 μg misoprostol vaginally and 4 placebo tablets sublingually.

The dose and route of administration of misoprostol will be blinded to the women. Side-effects will be recorded at hourly intervals up to 3 hours after misoprostol administration. The preliminary outcome will be assessed before the woman leaves the clinic. The final outcome regarding the efficacy, side-effects since treatment and acceptability will be assessed at the follow-up visits on Day 15 and Day 42 of the study unless women are still bleeding and require a further follow-up.

This multinational trial will be carried out in 16 departments of obstetrics and gynaecology of teaching hospitals. All departments provide routine abortion services and also carry out clinical research. The trial will be conducted according to ICH-GCP guidelines and the investigators are trained to carry out research accordingly.

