The main efficacy analysis will include all women randomized for whom outcome is known. Criteria for exclusion from per-protocol analysis are the following: essential data are missing from the participant's records making it impossible to judge treatment outcome (same as for main analysis); any violation of the study protocol, including violation of eligibility criteria; and treatment non-compliance.

At each of the participating centres, eligible women will be allocated randomly using blocks of variable size to the four treatment groups using computer-generated random tables. These tables will be produced by the Programme's Statistics and Informatics Services Team. Each participating woman will have two medicine packs: one for Day 1 of the study containing one tablet of 200 mg of mifepristone; and the other for Day 2 of the study (24 hours later) containing 4 tablets to be taken vaginally (either 4 placebo tablets in groups A and B, or 2 misoprostol and 2 placebo tablets in group C, or 4 misoprostol tablets in group D); and 4 tablets to be taken sublingually (either 2 tablets of misoprostol and two placebo tablets in group A; or 4 misoprostol tablets in group B; or 4 placebos in groups C and D). The misoprostol tablets and placebo tablets will be packed in blisters. On the blisters it is indicated which tablets are taken vaginally and which tablets are taken sublingually. All subjects will have the same number of tablets administered vaginally and sublingually. We will use mifepristone (Exelgyn) and misoprostol (Pfizer) tablets which are available in many European countries.

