### Study procedures

Before admission to the study potential subjects will undergo the following: ultrasound examination to verify the length of the pregnancy and check that the pregnancy is intrauterine. If the pregnancy is more advanced, if there is a suspicion about an abnormal pregnancy (e.g. extrauterine, molar pregnancy, etc.) the woman will not be admitted to the study; haemoglobin measurement; the blood group and Rh typing according to the routine of the centre; full medical, obstetrical and gynaecological history; full medical and gynaecological examination including pelvic examination, height, weight and blood pressure; and bacteriological examination according to the routine of the centre.

Women who fulfil the criteria for admission and who are willing and able to participate in the trial and have given their informed consent will be included in the study. Women admitted to the study will be given a diary card to record days and amount of vaginal bleeding and side-effects. The card will also give the dates of the follow-up visits. The day of start of the treatment will constitute the day of formal admission to the study (i.e. Day 1 of the study) when the length of pregnancy should not be more than 63 days. The tablet of mifepristone must be swallowed in the presence of a member of the study team who will record on the data form the date and time when the tablet was taken.

All centres will have subject numbers from 1–192. As we plan to take randomly 4 packs of tablets per centre for quality control, each centre will recruit 188 women for the study. To ensure an equal representation of women with longer duration of pregnancy (beyond 49 days) at each centre, subject numbers will be divided between each category of gestational length so that the numbers 1–64 are used for women with the duration of pregnancy up to 49 days, 65–128 for 50–56 days and 129–192 for pregnancies of 57–63 days.

After the admission visit on Day 1 all subjects will attend the clinic on three occasions during the course of the study.

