### Data management

Participating centres will be requested to record the data on paper data collection forms, enter them and send them electronically on a weekly basis to Geneva, using a Web-based system [14]. Recruitment and data quality will be monitored by the Programme's Statistics and Informatics Services Team using this system.

Data will be analyzed centrally in Geneva. Descriptive statistics will be calculated for all baseline characteristics for all subjects randomized, by treatment group, to describe characteristics of the population and to assess comparability of the groups. The overall summary statistics for women who complete the trial will be compared with those for the subjects lost to follow-up.

All subjects randomized having known outcome will be included in the main efficacy analysis in their randomized groups. If attempts fail to locate and contact a woman lost to follow-up, and her outcome of treatment is not known, then that woman will be excluded from the efficacy analysis. If she has information on side effects, she will be included in the safety analysis. Baseline characteristics of women lost to follow-up will be compared with those completing the study and between groups, to explore the possibility of bias due to these differences.

Crude rates for each outcome will be calculated in each arm and exact confidence intervals based on the binomial distribution calculated as described in Armitage and Berry [15]. If the interaction of misoprostol route by misoprostol dose is significant at 5% level, comparisons will be made between routes for each dose and between doses for each route. If the interaction is not significant at 5%, two comparisons will be made, between routes for the two doses combined, and between doses for the two routes combined. For these comparisons, relative risks (RR) of failure to achieve a complete abortion and failure to terminate pregnancy and the two-sided 95% CIs will be calculated by standard methods, as well as risk differences and two-sided 95% CIs. The latter will be used to test the non-inferiority hypotheses (at 2.5% level of significance) for achieving complete abortion.

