Stratified analysis for efficacy will be conducted by gestational age (up to and including 49 days, 50–56 days and 57–63 days). Adjusted analysis by centre and for any prognostic variable showing imbalance at baseline will be performed using Mantel-Haenszel approach and/or logistic regression where appropriate. A per-protocol analysis will be performed excluding women with conditions as described in earlier sections. Efficacy will also be calculated excluding subjects with undetermined outcome. Survival analysis if appropriate will be used to compare the differences in induction-abortion intervals. Chi-square test or Fisher exact test as appropriate, will be used to compare the proportion of women with each side-effect, adjusting for multiple inferences with an appropriate technique.

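### The deciding risk-difference interval does not mention the randomisation strata, and the supportive adjusted analysis picks covariates by observed imbalance: a small, wording-only improvement

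*Protocol article*

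**What the plan says.** All references are to the protocol article.

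- **Design.** Methods/design calls the trial "randomized, stratified by centre and by the length of gestation", with three gestational bands. Study procedures carries this out within each centre: "subject numbers will be divided between each category of gestational length", 64 numbers per band. Allocation uses blocks of variable size across the four groups.
- **Deciding interval.** Data management plans relative risks and intervals: "the two-sided 95% CIs will be calculated by standard methods, as well as risk differences and two-sided 95% CIs". It continues: "The latter will be used to test the non-inferiority hypotheses (at 2.5% level of significance) for achieving complete abortion". Neither sentence mentions centre or gestational band.
- **Analyses that use the strata.** Later in Data management: "Stratified analysis for efficacy will be conducted by gestational age". Then: "Adjusted analysis by centre and for any prognostic variable showing imbalance at baseline will be performed using Mantel-Haenszel approach", with logistic regression as an addition or alternative. No effect measure is given for the adjusted analysis, and neither analysis is linked to the 3% margin.
- **Margin.** Number of subjects and statistical power sets 3% on the difference in complete abortion rates, 800 μg minus 400 μg.

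**The concern.** Two separate matters arise.

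1. **The strata and the deciding interval.** If complete abortion rates differ by gestation or centre, stratified randomisation removes that variation from the treatment comparison. An interval that ignores the strata still counts it as noise and is slightly too wide. On the natural reading the deciding interval is of this kind. If it were already stratified, there would be little reason to list the band-stratified and centre-adjusted analyses separately.

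2. **The supportive adjusted analysis.** After proper randomisation, baseline imbalance is chance. A rule that adjusts for whatever turns out imbalanced, with no variables and no threshold named, lets the draw decide the model. If the result is a logistic odds ratio, it is also on a different scale from the margin.

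The stakes are a little precision in a decision that turns on one confidence limit, and supportive results that may be hard to compare with the primary one when that limit falls close to 3 points.

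**Working it through.** **Inputs from the article.** 16 centres × 3 bands = 48 cells; 64 numbers per cell over four groups, so 64/4 = 16 per arm per cell; complete abortion 95% in both groups; margin 0.03; about 680 per group, 720 after loss; two-sided 95% interval (one-sided 2.5%) in Data management.

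**Assumed, not in the article.** How far rates differ between bands and centres.

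**1. The plan's own figure.** Farrington-Manning sample size with null-restricted rates 0.961/0.931:

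n = [z₁₋α√v₀ + z₁₋β√v₁]² / 0.03², with v₀ = 0.961×0.039 + 0.931×0.069 ≈ 0.1016 and v₁ = 2×0.95×0.05 = 0.095.

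At one-sided 5% and 80% power: (1.645×0.3188 + 0.842×0.3082)² / 0.0009 ≈ 683, against the stated 680. No stratum enters, so the sample size does not rest on a stratified analysis. The figure reproduces at one-sided 5%, not 2.5%. That is a separate matter, but it is why the power figures in step 4 start near 0.75.

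**2. Share of variance lying between strata**, Var(p_s) / [p(1−p)], with p(1−p) = 0.0475:

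| Assumed spread of failure | Calculation | Share |
|---|---|---|
| Bands 3/5/7% | 0.000267/0.0475 | 0.56% |
| Bands 2/5/8% | 0.000600/0.0475 | 1.26% |
| Centre SD 2 points | 0.0004/0.0475 | 0.8% |
| Centre SD 3 points | 0.0009/0.0475 | 1.9% |
| Centre SD 4 points | 0.0016/0.0475 | 3.4% |

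Adding the low ends gives about 1.4%; adding the high ends gives about 4.6%.

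**3. Effect on the interval.** Half-width at 680 per group: 1.96×√(2×0.0475/680) = 0.0232, or 2.3 points. Removing 1.4% of the variance narrows it by 0.0232×(1−√0.986) ≈ 0.02 points. Removing 4.6% narrows it by 0.0232×(1−√0.954) ≈ 0.05 points.

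**4. Simulation.** 48 equal cells, 20,000 replicates, 15 per arm per cell (720 per arm) or 30 (1440, pooled over routes). With equal cells the crude and stratified point estimates coincide, so only the standard error differs. The stratified variance is Σ[p₁(1−p₁)+p₂(1−p₂)]/(n−1) over cells, divided by 48². Probability of declaring non-inferiority at a true difference of 0, crude → stratified:

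| Assumed cell rates | 720 per arm | 1440 per arm |
|---|---|---|
| All 95% | 0.748 → 0.746 | 0.958 → 0.959 |
| 89–98% | 0.734 → 0.735 | 0.953 → 0.954 |
| 80–99% | 0.685 → 0.695 | 0.937 → 0.940 |
| 67–99.6% | 0.637 → 0.664 | 0.909 → 0.920 |

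At a true 3-point difference the false-claim rate is 0.024–0.027 crude and 0.026–0.029 stratified. A further simulation with the Sato variance, again under assumed heterogeneity, gave a variance reduction of about 1–2.5%, a power gain of at most about 1 point, and a false-claim rate of 2.5–2.7% with either interval.

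**5. The scale.** The odds ratio equal to a 3-point loss is [(p−0.03)/(1.03−p)] / [p/(1−p)], where p is the 800 μg rate:

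- p = 90%: (0.87/0.13)/(0.90/0.10) = 0.744
- p = 95%: (0.92/0.08)/(0.95/0.05) = 0.605
- p = 98%: (0.95/0.05)/(0.98/0.02) = 0.388

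Conversely, an odds ratio of 0.605 means a loss of 5.5 points at 90%, 3.0 at 95% and 1.3 at 98%. There is no fixed translation to the margin.

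**The case against.** The strongest reply is that the plan already does what matters. Band and centre are both analysed unconditionally; only further prognostic variables depend on imbalance. Mantel-Haenszel is offered alongside logistic regression and can itself give a risk difference, and a logistic model can be standardised to one. The 3% test is placed on the risk difference and nowhere else, so no covariate choice enters the decision. The article nowhere says the deciding interval is unstratified, and choice of estimator is commonly left to a fuller protocol or analysis plan, neither of which is shown. A simple risk difference after stratified randomisation is valid, and with about 16 women per arm per cell, a 5% failure rate gives only 16×0.05 = 0.8 expected failures, so stratification is not free of awkwardness.

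Most of this stands, and it rules out several stronger readings that a reader might infer:

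- *That the primary interval is invalid or favours a false claim.* The simulations show the opposite tendency: it is at most slightly conservative.
- *That all adjustment hangs on imbalance or on logistic regression.* The text does not say so for band, centre or method.
- *That post hoc covariates could decide non-inferiority.* The adjusted analyses are not tied to the margin.

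The reply does not remove two things. The article describes the deciding interval and places the strata elsewhere, so the natural reading is a crude interval. And the imbalance trigger is a rule the article states; it is not a detail left for later. Sparse cells call for a suitable variance, such as Sato's; they do not rule out stratifying.

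**Conclusion.** The point holds as a small improvement. That the deciding interval is crude is inferred from the layout of Data management; it is not stated there. If it is crude, it remains valid, with variance overstated by roughly 1 to 4% (4.6% with both assumed ranges at their upper ends) and a cost of about 1 point of power or less. Only an extreme spread of cell rates, 67–99.6%, costs nearly 3 points (0.637 against 0.664). All these sizes rest on heterogeneity that the article does not give.

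The imbalance rule is data-dependent, and an odds ratio cannot be set directly against the margin, but both affect supportive results only. The case for changing the text is that it fixes the analysis in advance at no cost. The gain in precision is minor, and the primary conclusion is not in error.

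**What to change.** In Data management:

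1. Where the non-inferiority interval is defined, make the primary estimate the Mantel-Haenszel risk difference stratified by centre and gestational band (up to 49, 50–56, 57–63 days), with a Sato-type two-sided 95% interval, and use that interval for the 3% decision.
2. In the adjusted-analysis sentence, replace the imbalance trigger with a list of covariates named in advance.
3. State that adjusted results are reported as risk differences, with the crude difference and any odds ratios as supportive.

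The cost is wording only. No new data, visits or participants are needed, because centre and band are already recorded as part of the randomisation.

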The results of our recent study [13] demonstrate an equivalent efficacy for both 24 h and 48 h intervals when 800 μg misoprostol is administered vaginally after mifepristone. As 24 h interval is more practical it is likely to become the standard in mifepristone-misoprostol regimens. This is why we chose the 24 h interval for the present trial.

The ultimate goal of our research is to improve the methods for termination of early pregnancy. The main objective of the present randomized trial is to compare four misoprostol regimens when administered either sublingually or vaginally 24 hours after 200 mg of mifepristone, among women with a gestational age of up to 63 days. The four regimens will be compared in respect of the following main outcomes: (i) their efficacy to induce complete abortion; (ii) induction-to-abortion interval, when possible; (iii) the occurrence of side-effects; and (iv) women's perceptions.

Although there are no comparative studies the efficacy might be somewhat lower if the dose of misoprostol is reduced. If, however, the side-effects will decrease and the regimen is more acceptable to women, it would be justified to use a lower dose if non-inferiority is demonstrated within a margin of 3%. Our hypothesis is that the efficacy of 400 μg misoprostol, whether given sublingually or vaginally after mifepristone pretreatment, is not inferior to that of 800 μg misoprostol within a margin of 3%.

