#### Incidence of side-effects

Signs and symptoms will be recorded at admission, and women will keep daily records of any complaints and medication taken, for the duration of the whole trial and report them at each visit. Data on signs and symptoms will be collected prior to misoprostol administration and immediately after administration as well as at one-hour intervals up to three hours. In addition, the intensity of side effects is recorded indicating whether side-effects were mild, moderate or severe. However, the pain is recorded using the scale from 0–10, in which 0 means no pain and 10 is the worst possible pain the subject can imagine.

We classify the signs and symptoms that women may have during the trial as follows: Pregnancy-related symptoms: such as nausea, vomiting, breast-tenderness, fatigue, dizziness, headache and fainting; Drug-related side-effects, such as diarrhoea, fever and rash; and side-effects related to the abortion process, such as lower abdominal pain and bleeding.

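### The only side-effect test the article states compares proportions and makes no use of the pre-misoprostol readings, intensity grades or 0–10 pain scores, so it is less sensitive than the collected data allow

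*Protocol article*

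**What the plan says.** The Data management section of the protocol article gives the side-effect analysis in one sentence: "Chi-square test or Fisher exact test as appropriate, will be used to compare the proportion of women with each side-effect", and the same sentence ends with "adjusting for multiple inferences with an appropriate technique". No other side-effect analysis is stated.

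The section Incidence of side-effects describes richer data:
- **Timing:** "Data on signs and symptoms will be collected prior to misoprostol administration and immediately after administration", and then hourly to three hours.
- **Severity:** "the intensity of side effects is recorded indicating whether side-effects were mild, moderate or severe".
- **Pain, handled separately:** "the pain is recorded using the scale from 0–10".

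The same section has a class of "Pregnancy-related symptoms: such as nausea, vomiting, breast-tenderness, fatigue, dizziness, headache and fainting". It lists diarrhoea, fever and rash separately as drug-related, and lower abdominal pain and bleeding as part of the abortion process.

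The Background says efficacy might be somewhat lower at the reduced dose and then gives the condition under which that would be acceptable: "If, however, the side-effects will decrease and the regimen is more acceptable to women", together with non-inferiority within 3%.

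**The concern.** Side-effects are one of the four main outcomes and form part of the benefit that would justify the lower dose. The route comparison is also open, since the Background reports more side-effects with sublingual use in an earlier study.

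A comparison of proportions has two weaknesses here.

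- **Symptoms already present.** A woman who is nauseated before misoprostol may be counted as having nausea whichever regimen she receives. Such women add noise and shrink the difference between groups. The article does not say whether having a side-effect means any occurrence or onset after misoprostol.
- **Severity.** A proportion does not show a shift from severe to mild. If nearly all women have some pain, the proportion with any pain is close to its ceiling and moves little even when scores fall.

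At stake is the sensitivity of the comparison: a real reduction with the lower dose, or a real excess with one route, could be missed although the data to detect it were collected.

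**Working it through.** **No planned figure to reproduce.** The article gives no power, rates or standard deviation for side-effects. Only the numbers of women come from it. Everything else below is assumed, at two-sided 5% and before any multiplicity adjustment, which would lower every power shown.

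**Women per dose, routes combined** (Number of subjects and statistical power)
- From the efficacy calculation: 2 × 680 = 1360.
- From planned recruitment: 16 × 188 = 3008; 3008 / 4 × 0.95 = 714 per group; 2 × 714 = 1428. The 5% allowance is for efficacy outcomes, so in-clinic side-effect data may be more complete, up to 3008 / 2 = 1504.

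**Formulas**
- Two proportions: power = Φ(|p1 − p2| / √[(p1(1 − p1) + p2(1 − p2)) / n] − 1.96).
- Two means: power = Φ(d / (SD × √(2/n)) − 1.96).

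**1. Symptoms present before misoprostol (n = 1360).** Assume onset after misoprostol in 30% versus 25% of women who were symptom-free beforehand, and a share b already symptomatic and counted in both arms.

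For b = 40% the crude proportions are 0.40 + 0.60 × 0.30 = 0.58 and 0.40 + 0.60 × 0.25 = 0.55. The standard error is √[(0.2436 + 0.2475) / 1360] = 0.0190, so power = Φ(0.03 / 0.0190 − 1.96) = 35%. Among the 816 per dose who were symptom-free, the standard error is √[(0.21 + 0.1875) / 816] = 0.0221, so power = Φ(0.05 / 0.0221 − 1.96) = 62%.

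| b | Crude occurrence | Among women symptom-free beforehand |
|---|---|---|
| 0 | 83% | 83% |
| 20% | 56% | 74% |
| 40% | 35% | 62% |
| 60% | 21% | 46% |

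The gain from using the earlier reading is the difference along a row. The drop from 83% down the crude column is not all recoverable.

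This table takes an unfavourable case, in which every symptomatic woman is counted whatever happens later. A milder case was simulated with 1428 per dose: 35% symptomatic beforehand, log-odds ratio 1.8 for the earlier reading and −0.22 for dose. The chi-square test had 71% power and the adjusted logistic model about 76% (400 runs; Monte Carlo standard error of the first figure √[0.71 × 0.29 / 400] = 2.3 points). The gain is modest.

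**2. Pain (n = 1360, mean 5, SD 2.5).** For a difference of 0.3 points:
- Scores: 0.3 / (2.5 × √(2/1360)) = 3.13, so power = Φ(3.13 − 1.96) = 88%.
- Any pain, taken as a value above 0.5: Φ(4.5/2.5) = 96.4% versus Φ(4.2/2.5) = 95.4%, power 28%.

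| Difference | Scores | Median split | Any versus none |
|---|---|---|---|
| 0.2 | 55% | 38% | 15% |
| 0.3 | 88% | 70% | 28% |
| 0.4 | 99% | 91% | 46% |

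A simulation with scores rounded and limited to 0–10, 1428 per dose and a 0.25-point difference (1,000 runs) gave 78% for scores and 22% for any versus none. The mean formula gives Φ(0.25 / (2.5 × √(2/1428)) − 1.96) = 76%, in line with it.

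**If the dose-by-route interaction is significant,** the plan compares doses within each route at about 680 per group, and power falls for every method. For 30% versus 25% it is 54% instead of 83%.

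**The case against.** The strongest reply is that this is a condensed article and a statistical analysis plan may well say how grades, pain scores and earlier readings are used. That limits the point. A reader might infer that the trial will ignore or discard these data, or reduce pain to yes or no. The documents do not support either inference: the article nowhere excludes the data, it describes pain separately, and it leaves undefined what counts as having a side-effect, which could mean onset after misoprostol or a severity threshold. The any-versus-none pain figures therefore show what would be lost if pain were analysed that way, not what the plan prescribes.

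A reader might also infer that the stated test is biased or unadjusted. It is neither. A chi-square or Fisher test between randomised groups is valid, and the plan corrects for multiplicity. The Data management section also has "Adjusted analysis by centre and for any prognostic variable showing imbalance at baseline will be performed using Mantel-Haenszel approach and/or logistic regression". It follows a sentence on efficacy and names no outcome, so it could be read to cover side-effects. Even so, it reaches only centre and variables that happen to be imbalanced, and it names neither the pre-misoprostol symptom readings nor the grades or pain scores.

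Other limits also stand. The argument about earlier symptoms applies to the pregnancy-related class; nothing in the article suggests that diarrhoea, fever or rash are common before misoprostol. The article gives no prevalence for any symptom. Nothing shows that a 0.25- or 0.3-point pain difference matters clinically. The case for the lower dose also rests on acceptability, which is assessed by questionnaire.

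What remains is that the article does name a method, and for a main outcome it is less sensitive than the data already being collected allow.

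**Conclusion.** The point holds as one of efficiency and clarity, not of error. The stated test is valid and multiplicity-adjusted, but it makes no use of the pre-misoprostol reading, the grade or the pain score, and so gives up sensitivity for pregnancy-related symptoms and for pain.

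The direction is firm; the size is not, because every rate, effect and standard deviation is assumed. Baseline adjustment brings a modest gain in the simulated case (about 71% to 76%). It brings more if many women are symptomatic beforehand and all of them are counted as affected (35% to 62% at 40%). For pain the gain is large only if the alternative is any versus none: about 22% to 28% against 78% to 88% for a 0.25- to 0.3-point difference with SD 2.5. All of this assumes doses compared with routes combined and no multiplicity adjustment.

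**What to change.** State the following before the data are examined.

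- **Symptoms that can be present before misoprostol:** compare groups with a logistic model, or an ordinal model where grades are used. Include dose, route, the pre-misoprostol reading of that symptom, and the randomisation strata (centre and gestational age). Handle the dose-by-route interaction as the Data management section does: test it first, and compare doses within each route, and routes within each dose, if it is significant at 5%. Adjusting for this reading is sound although it follows allocation, because all women have then had the same mifepristone treatment and the regimens have not yet diverged.
- **Pain:** compare the maximum 0–10 score over the three hours after misoprostol by analysis of covariance with the pre-misoprostol score, treating dose, route and their interaction in the same way.
- **Proportions:** keep them, with the chi-square or Fisher test and the multiplicity adjustment, alongside the models. Say whether a side-effect means any occurrence or onset after misoprostol.

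The cost is a little more analysis work. No new data or visits are needed.
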